### Laboratory methodologies

Breast milk will be manually expressed by trained nurses or by the mothers themselves after cleansing of the breast skin. Feces will be collected from the diaper using a sterile plastic spatula. All biological samples will be collected in sterile containers and immediately frozen at −80 °C (samples collected during hospital stay and study visits), or at −20 °C for samples collected at home (neonatal feces during follow up) and subsequently transferred at −80 °C. This will allow to minimize alterations of IgA pool and microbiota composition. For experimental analysis samples will be defrosted in batches, always with an equal number of samples between experimental groups.

IgA quantification in breast milk will be performed with commercially available ELISA kit (Invitrogen, cat. BMS2096), in technical duplicates and including a standard curve in each 96-well plate. Breast milk samples will be devoid of fat components by centrifugation and appropriately diluted in assay diluent. Feces will be defrosted, suspended in PBS with 0.1 mg/ml of trypsin inhibitor from soybean (Sigma Aldrich) at a concentration of 100 mg/ml, and homogenized through shaking at 30 Hz for 20 s in a tissue lyser (Qiagen), after the addition of 1.4 mM ceramic beads (MP Biomedicals). Then they will be centrifuged at 50 × *g* for 10 min to remove debris, and supernatant will be diluted 1:5 with assay diluent.

For magnetic-activated cell sorting (MACS) of IgA-coated and non-coated bacteria, defrosted, homogenized, and diluted pellets will be slowly centrifuged (50 × *g* for 10 min, 4 °C) to remove large particles, leaving bacteria in suspension. Supernatants will be collected and spun down at 4000 × *g* × 10 min (4 °C) to retrieve bacterial pellets, that will be then resuspended in MACS buffer, blocked with anti- CD16/32 solution in MACS buffer (20 min, 4 °C) and stained with anti-human IgA PE-conjugated antibody (clone mA-6E1, 1:100) for 30 min at 4 °C. After appropriate washing steps, stained pellets will be incubated in 1 ml staining buffer containing 50 μl Anti-PE Magnetic Activated Cell Sorting (MACS) beads (Miltenyi Biotec). This solution will then be sorted by MACS through LS columns (Miltenyi) to separate IgA^+^ and IgA^-^ fractions of fecal microbiota. For sequencing of bacteria from feces and milk, DNA will be extracted withDNeasy PowerSoil Pro Kit (Qiagen, cat. 47019) and sequenced by shotgun metagenomics on the Illumina HiSeq 2500 platform by Prebiomics S.r.l., Trento, Italy. The quality of raw sequencing data will be assessed using MultiQC (v1.11).^27^ Host contaminant reads (human DNA) will be filtered out using KneadData (v0.10.0) with Bowtie2 (v2.5.4)^28^ against the GRCh38 genome reference database. Taxonomic profiling will be performed using MetaPhlAn (v4.0.6), and functional profiling will be conducted using HUMAnN (v3.9). For downstream analysis, the QIIME2 platform (v2024.10) will be employed.^29,30^ Alpha and beta diversity metrics will be calculated with the qiime diversity core-metrics-phylogenetic command. Shannon Entropy will be used as representative metrics for alpha diversity, with Box and Whisker plots generated in GraphPad Prism (v10.2.3). BrayCurtis dissimilarity will be used as a representative metric for beta diversity, and a Principal Coordinate Analysis (PCoA) plot will be generated in R (v4.3.1) using the “ggplot2” library.

Chemokine CCL28 will be measured on maternal serum and breast milk with commercially available ELISA kit (Bio-Techne, cod. DY717). Appropriate negative and positive controls will be carried on throughout all the protocol steps.

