### Data collection, sample size and statistical analysis

Demographic and clinical data will be collected prospectively in an electronic database (Excel software, Microsoft Corp.), where enrolled patients will be de-identified and associated with a single numerical code. The database will be stored on the Institutional server and encrypted according to standard internal protocols for data protection.

According to internal historical data, an average of 1.5 women per week is expected to receive prolonged ABX therapy immediately before delivery at the study site. Based on preliminary animal data, an average drop of approximately 30% in breast milk IgA can be expected after prenatal ABX treatment. Considered an average content of IgA of 3.8 g/L (S.D. ± 1 g/L), a sample size of around 34 women per group would be enough to detect a prudential difference of 20% with a power of 0.9 and an Alpha equal to 0.05. We would like to account for a dropout rate of 20%. Therefore, a sample size of 41 women per group (ABX-treated vs. controls) would be appropriate and feasible within one year in our clinical context.

Results will be represented using box plots showing the interquartile range, with a single data point per subject. Statistically significant differences between two groups will be evaluated with Mann-Whitney two-sided unpaired U-test, for non-normally distributed data (visually checked), or two-sided unpaired *t*-test for normally distributed data. In case of longitudinal experiments (e.g., IgA concentration over time in the same subjects), repeated-measures ANOVA will be applied. A probability value of **p* < 0.05 will be considered as significant. Data analysis and graphing will be performed using GraphPad Prism (GraphPad software) vers. 9.0.1, and StataMP vers. 17.0 (Stata Corp.).

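### Defrosting batches are balanced by exposure group but the named group tests ignore batch, so any batch variance left after calibration makes them conservative and forgoes some precision

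*Protocol article*

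**What the plan says.** Under Laboratory methodologies, samples are thawed for analysis in batches, "always with an equal number of samples between experimental groups". For breast milk IgA the ELISA is run "in technical duplicates and including a standard curve in each 96-well plate". No calibrator is described for fecal homogenisation, magnetic sorting of IgA-coated bacteria, DNA extraction or sequencing. The section closes by promising negative and positive controls across the protocol steps.

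Under Data collection, sample size and statistical analysis, "Statistically significant differences between two groups will be evaluated with Mann-Whitney two-sided unpaired U-test, for non-normally distributed data", or a "two-sided unpaired *t*-test for normally distributed data". For longitudinal outcomes "repeated-measures ANOVA will be applied". None of these carries a batch term. On display, "Results will be represented using box plots showing the interquartile range, with a single data point per subject".

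The article gives no number of batches, batch size or batch variance. Its planning SD for milk IgA, 1 g/L, is not split into between-woman and assay parts.

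**The concern.** Equal numbers per group in every batch is a blocked layout. A shift common to one batch moves both groups alike and cancels from the difference in means. An unpaired t-test or Mann-Whitney test does not use this: it counts the spread between batches as within-group noise. The reported standard error then describes a less precise experiment than the one run.

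At stake is efficiency. The study takes the trouble to balance its batches, and the stated tests do not collect the benefit. More than one batch is to be expected. One visit's milk IgA samples from 41 + 41 women in duplicate need 82 × 2 = 164 wells, more than one 96-well plate before any standards. The section Timing of analysis also spreads the work over four three-month periods, one every six months.

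The point concerns the exposed-versus-control contrast at a single visit. It does not concern assay timing being mixed with visit.

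**Working it through.** **Inputs from the article.** Mean 3.8 g/L, SD 1 g/L, difference 20% (0.20 × 3.8 = 0.76 g/L), about 34 women per group before dropout, 41 enrolled, two-sided tests at 0.05.

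**Assumed, because not given.** Batch share of variance ρ (range 0 to 0.30) and number of balanced batches B (2, 4 or 8).

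**The plan's own figure.** n = 2(1.960 + 1.282)² / 0.76² = 36.4, so 37 per group (38 with the t distribution). At 34 per group, power is 0.88 by the normal formula and 0.87 by the t distribution. The stated 34 is reproduced only if the difference is rounded to 0.8 g/L. That is a separate point and nothing below depends on it. The baseline here is 0.87 at 34 per group. After 20% dropout, 41 × 0.8 = 32.8, so about 33 are evaluable.

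**Standard error.** With total variance 1 and equal batches:

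- True variance of the group difference: 2(1 − ρ)/n, because the batch part cancels.
- Expected variance reported by the unpaired test: (2/n) × [(1 − ρ) + ρ × n/(n − 1) × (1 − 1/B)].
- Ratio of the standard errors: √[1 + ρ/(1 − ρ) × n/(n − 1) × (1 − 1/B)].

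For n = 34:

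| ρ | B = 2 | B = 4 | B = 8 |
|---|---|---|---|
| 0 | 1.00 | 1.00 | 1.00 |
| 0.10 | 1.03 | 1.04 | 1.05 |
| 0.20 | 1.06 | 1.09 | 1.11 |
| 0.30 | 1.10 | 1.15 | 1.18 |

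For example, at ρ = 0.20 and B = 4: √(1 + 0.25 × 34/33 × 0.75) = √1.193 = 1.09. The ratio does not depend on the unit of measurement, so it applies to any outcome with that batch share.

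**Power and type I error.** Simulation with 8,000 runs per setting, 34 per group and four or eight balanced batches, comparing the unpaired t-test with a linear model containing group and batch. Power is for a difference of 0.76 g/L.

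| ρ | SD of 1 includes batch: unpaired / with batch | Batch on top of SD 1: unpaired / with batch | Type I error, unpaired t (SD of 1 includes batch) |
|---|---|---|---|
| 0 | 0.87 / 0.87 | 0.87 / 0.87 | 0.05 |
| 0.05 | 0.88 / 0.89 | 0.86 / 0.87 | 0.045–0.047 |
| 0.10 | 0.89 / 0.90 | 0.85 / 0.87–0.88 | 0.042–0.043 |
| 0.20 | 0.90–0.91 / 0.93 | 0.82–0.83 / 0.87–0.88 | 0.030–0.032 |
| 0.30 | 0.91–0.92 / 0.95–0.96 | 0.78–0.79 / 0.87 | 0.022–0.029 |

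The simulated standard errors agree with the formula. At ρ = 0.20 (SD of 1 including batch) the unpaired test reports 0.236 to 0.239 against a true SD of the difference of 0.214 to 0.219. The Mann-Whitney test behaves alike, with type I error about 0.030 at ρ = 0.20.

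With only two batches the effect is smaller. For 33 per group split 20 + 20 and 13 + 13 at ρ = 0.20, the standard error is about 5% too large, type I error about 4%, and power about 0.91 against 0.92.

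**What these shares mean for milk IgA.** With SD 1 g/L, ρ = 0.10 is a residual batch SD of √0.10 = 0.32 g/L (0.32/3.8 = 8% of the mean), and ρ = 0.20 is √0.20 = 0.45 g/L (12% of the mean). Both would have to remain after plate calibration.

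**The case against.** **The loss is conditional.** It depends on a batch variance that the article does not give, and it is nil when that variance is zero. This stands, and the conclusion is worded accordingly.

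**Milk IgA is the best protected outcome.** The power figures use the milk IgA planning values, and that assay has duplicates and a standard curve on each plate. A residual batch SD of 12% of the mean is not supported by anything in the article. This also stands: the milk IgA effect is probably small. The curve does not correct for thawing, defatting or dilution, and none is described for the fecal and sequencing steps. The promised positive and negative controls can reveal a failed run, but the text does not say that they are used to adjust values.

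**A reader might infer that power falls below plan.** The documents do not support this. If the SD of 1 g/L already includes assay variation, unpaired power rises slightly with ρ, and only a further gain is forgone. Power drops only if batch variance comes on top of that SD, and the article does not say which applies.

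**A reader might infer that displayed error bars are too wide.** None are planned. The display is box plots with the interquartile range, so the effect is on standard errors, any intervals and p-values.

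**Balance is stated for defrosting batches only.** Nothing says that plates, magnetic sorts or the outsourced sequencing runs are balanced by group. The argument cannot simply be carried over to them.

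**A condensed article may leave technical covariates to a fuller plan.** This is fair in general. Here, however, the article itself names the tests, and those tests do not follow the layout it fixes.

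**Conclusion.** The mismatch is real: a layout balanced within defrosting batch, analysed by tests that ignore batch. Its consequence is conservative. The group difference is unbiased, and the type I error falls below 5% if batch variance remains.

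With 33 to 34 women per group and two to eight batches (assumed), the loss is nil at a batch share of 0 and about 1 to 2 power points at 0.1. At 0.2 it is about 1 to 3 points if the SD of 1 g/L includes batch variation and up to 5 points if it does not, with a standard error about 5 to 11% too large and type I error about 3 to 4%.

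The case is weak for milk IgA. It is stronger for fecal IgA, the IgA-coated fractions and Shannon diversity, where no calibrator is described, although the article gives no variance from which to compute a power figure for these.

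This is a cheap improvement of low to moderate priority. It gives no reason to doubt the validity of the planned comparison.

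**What to change.** - Record the defrosting batch of every sample in the study database.
- In the statistical section, state that univariate laboratory outcomes are compared between groups with the balanced defrosting batch as a blocking factor: a linear model with a fixed or random batch effect, or a van Elteren (batch-stratified Wilcoxon) test where ranks are used. Carry the batch term into the longitudinal model.
- If Bray-Curtis community data are tested between groups, use a permutation test with permutations restricted to within batch. Neither a univariate model nor a van Elteren test fits such data.
- State whether plates, sorts and sequencing runs keep the balance of the defrosting batches. Use them as blocks on this argument only where they do.

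**Cost.** One database variable, one or two sentences, and B − 1 degrees of freedom with a fixed batch effect: 1, 3 or 7 of the 2 × 34 − 2 = 66 for two, four or eight batches. If there is no batch effect, the price is negligible (power 0.87 either way at 34 per group). The batch number is easiest to capture when the samples are defrosted.

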### Data collection, sample size and statistical analysis

Demographic and clinical data will be collected prospectively in an electronic database (Excel software, Microsoft Corp.), where enrolled patients will be de-identified and associated with a single numerical code. The database will be stored on the Institutional server and encrypted according to standard internal protocols for data protection.

According to internal historical data, an average of 1.5 women per week is expected to receive prolonged ABX therapy immediately before delivery at the study site. Based on preliminary animal data, an average drop of approximately 30% in breast milk IgA can be expected after prenatal ABX treatment. Considered an average content of IgA of 3.8 g/L (S.D. ± 1 g/L), a sample size of around 34 women per group would be enough to detect a prudential difference of 20% with a power of 0.9 and an Alpha equal to 0.05. We would like to account for a dropout rate of 20%. Therefore, a sample size of 41 women per group (ABX-treated vs. controls) would be appropriate and feasible within one year in our clinical context.

Results will be represented using box plots showing the interquartile range, with a single data point per subject. Statistically significant differences between two groups will be evaluated with Mann-Whitney two-sided unpaired U-test, for non-normally distributed data (visually checked), or two-sided unpaired *t*-test for normally distributed data. In case of longitudinal experiments (e.g., IgA concentration over time in the same subjects), repeated-measures ANOVA will be applied. A probability value of **p* < 0.05 will be considered as significant. Data analysis and graphing will be performed using GraphPad Prism (GraphPad software) vers. 9.0.1, and StataMP vers. 17.0 (Stata Corp.).

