**Fig. 1 Fig1:**
[figure not shown]
Graphical overview of the study protocol and procedures. ASQ: Ages and Stages Questionnaires. CCL28: Chemokine (C-C motif) ligand 28.

Conditions for which women will be treated with prolonged antibiotics will include but will not be limited to prelabor or preterm-prelabor rupture of membranes (PROM or pPROM), preterm labor with or without PROM, urinary tract infections, clinical chorioamnionitis, pneumonia. An equal number of women and their neonates not exposed to prenatal antibiotics (any exposure during pregnancy) will be enrolled as controls. Case-control dyads will be matched for gestational age at delivery and at the start of antimicrobial treatment.

Inclusion criteria will be the expression of written informed consent by parents of the neonate, a maternal antibiotic treatment (any molecule) for at least 7 days consecutively after 32 weeks of gestational age (or the absence of exposure to any systemic antibiotic treatment during pregnancy for the control group), and the intention to breastfeed neonates as long as possible during the first year of life. Exclusion criteria will be the absence of written informed consent, the intention or medical need to formula feed exclusively (or the presence of significant maternal concerns about breastfeeding), a maternal antibiotic treatment shorter than 7 days, the presence of pre-existing maternal immune-mediated disorders (including chronic immunodeficiencies), a delivery at a gestational age <34 weeks and the administration of antibiotics to neonates after birth, within the first week of life.

The amount of IgA (in breast milk and neonatal feces), the composition of microbiota (in breast milk and neonatal feces), the proportion and profile of IgA-coated bacteria (in neonatal feces), and the concentration of the Chemokine (C-C motif) ligand 28 (CCL28, in maternal serum and breast milk) will be quantified after collection of samples during pre-planned study visits, at the following time points:during the first week of lifeat 1 month of lifeat 3 months of life

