at 8–12 months of life (or at the time of breastfeeding interruption), after the introduction of solid food in the infant’s diet. At the same timepoint, five domains (communication, fine motor, gross motor, problem-solving ability, and personal-social functioning) of infants’ neurodevelopment will be assessed through the administration of Ages and Stages Questionnaire-3 (ASQ-3), and infants’ growth will be evaluated (weight, length, head circumference). The research protocol was reviewed and approved by Comitato Etico Milano Area 2, Approval number 0007973. Written informed consent will be obtained from enrolled women and the fathers of enrolled neonates. The study protocol adheres to the STROBE checklist for case-control studies and was registered at ClinicalTrials.gov (protocol code: NCT05813184, registered on April 14, 2023).

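### Repeated-measures ANOVA is a poor fit for IgA over four visits when the plan itself expects 20% dropout, allows weaning and leaves the last sampling time open

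*Protocol article*

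**What the plan says.** The statistical section of the protocol article names the method for repeated outcomes, with IgA as its example: "In case of longitudinal experiments (e.g., IgA concentration over time in the same subjects), repeated-measures ANOVA will be applied". The preceding sentence covers comparisons of two groups. It assigns "Mann-Whitney two-sided unpaired U-test, for non-normally distributed data (visually checked") and otherwise a "two-sided unpaired *t*-test for normally distributed data". No alternative for non-normal data is attached to the longitudinal analysis.

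The Study design section sets four sampling times: the first week, 1 month, 3 months, and a last one "at 8–12 months of life (or at the time of breastfeeding interruption"). Eligibility asks for "the intention to breastfeed neonates as long as possible during the first year of life", so the duration of breastfeeding will vary between mothers. On attrition, the sample size paragraph says "We would like to account for a dropout rate of 20" per cent.

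The longitudinal analysis is central to the study. The Abstract lists IgA in milk and infant stool up to one year as the first result, and the Discussion presents follow-up through the first year as what earlier cohorts lacked.

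**The concern.** The named method and the design do not match in four respects.

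- **Balance.** The classical analysis needs a full set of visits. Dropout is planned for, and a mother who weans before 3 months has no scheduled 3-month milk sample.
- **Common times.** The ANOVA treats the last visit as one level of a time factor. With sampling allowed "or at the time of breastfeeding interruption", that level mixes very different stages of lactation, even among dyads with all four samples.
- **Distribution.** The authors provide for non-normal data in two-group tests but not in the longitudinal analysis.
- **Sphericity.** Visits run from the first week to 8–12 months, so equal variances of between-visit differences are doubtful. This affects the time and group-by-time tests, not the between-group main effect.

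At stake are samples collected and then left out, a group comparison that may be distorted by who stays to the end, and a fourth time point whose meaning differs from mother to mother.

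**Working it through.** **Inputs from the statistical section:** 34 women per group raised to 41; 20% dropout; mean IgA 3.8 g/L, SD 1 g/L; target difference 20%, that is 0.2 × 3.8 = 0.76 g/L; alpha 0.05, two-sided; power 0.9.

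**The plan's own figures.** 34 × 1.2 = 40.8, which gives the stated 41. The 34 itself is not reproduced: the normal formula gives 37 per group and the exact t-test 38. That is a separate matter, noted here only because it means the planned size holds no reserve.

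**Complete sets after dropout.** 41 × (1 − 0.20) = 32.8, about 33 per group. The other 41 − 33 = 8 per group would each have given one to three samples if they leave after the first visit (an assumption). A complete-case analysis would then drop about 8 to 24 collected samples per group for each sample type.

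**What weaning does.**
- Before the 3-month visit: one scheduled milk sample cannot be taken.
- After the 3-month visit: four milk samples exist, but the last may be taken at any age from just after 3 months to 12 months, a span of about 9 months.
- Stool: sampling does not depend on breastfeeding, so weaning removes nothing.

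**Could the comparison be biased?** The following illustration is by simulation. Assumptions: four visits, true difference −0.76 g/L at each, SD 1, equal within-subject correlation of 0.5 or 0.7, 400,000 women per group, and a logistic chance of dropping out at each later visit that depends on the previous IgA value.

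| Dropout (assumed) | Completers, control / exposed | Completer difference, correlation 0.5 / 0.7 |
|---|---|---|
| Unrelated to IgA | 81% / 81% | −0.76 / −0.76 |
| Moderately related to low IgA | 82–83% / 73% | −0.72 / −0.71 |
| Strongly related to low IgA | 80% / 65–66% | −0.67 / −0.65 |

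The attenuation in the last row is (0.76 − 0.67)/0.76 ≈ 12% to (0.76 − 0.65)/0.76 ≈ 14%. With no relation there is none.

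**How skewed is milk IgA likely to be?** On the planning figures the coefficient of variation is 1/3.8 = 0.263. Even a lognormal variable then has skewness CV³ + 3·CV = 0.018 + 0.789 ≈ 0.81, which is modest.

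**Power if only complete sets are analysed.** The between-group test of a repeated-measures ANOVA compares subject means over the visits. With four visits, the SD of a subject mean is √[(1 + 3ρ)/4]: 0.79 at ρ = 0.5 and 0.88 at ρ = 0.7. Exact t power for a constant 0.76 g/L is shown below. The counts of 26 and 20 assume a further 20% or 40% incomplete (32.8 × 0.8 = 26.2; 32.8 × 0.6 = 19.7).

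| Complete per group | ρ = 0.5 | ρ = 0.7 |
|---|---|---|
| 33 | 0.97 | 0.93 |
| 26 | 0.93 | 0.86 |
| 20 | 0.84 | 0.76 |

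**The case against.** A reader might infer three stronger things, and the documents support none of them.

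- **That the plan analyses only dyads with complete data.** It does not say so. Complete-case analysis is a property of the classical method; an ANOVA with subject as a factor can be fitted to unbalanced data. Rules for missing visits may stand in an analysis plan that is not shown, so their absence is no finding.
- **That skewed data are expected.** The article gives a fallback conditional on a visual check, and its planning figures imply only modest skew in milk IgA.
- **That power collapses.** Putting complete-case counts of 33, 26 and 20 through a single-visit t-test gives about 0.86, 0.77 and 0.65. This is the wrong yardstick. The plan's separate two-group test needs no other visit and keeps every first-week sample (up to 41 per group, power 0.925). The ANOVA's own between-group test averages over visits and does better than those figures.

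It is also fair to say that bias needs dropout related to IgA or differing by exposure, and nothing in the article says that it will be. Women with marked concerns about breastfeeding are excluded, which should limit early weaning. A mixed model does not remove selection by weaning either: after weaning there is no milk to measure.

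These points limit the size of the concern but do not remove it. The method is named, not left open, and the last visit has no common time whatever is done about missing data.

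**Conclusion.** The mismatch between method and design holds. Classical repeated-measures ANOVA does not suit a schedule with 20% planned dropout, possible early weaning and a last sample at a variable stage of lactation, and it carries no stated option for non-normal data.

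The size of the harm is not established. About 33 of 41 dyads per group would have complete visits from dropout alone. Beyond that, the loss depends on a weaning rate that the article does not give. Bias is conditional: none if dropout is unrelated to IgA, and about 12–14% attenuation under the strongly differential dropout tabulated above, which is an assumption. Milk and stool also differ, since only milk is affected by weaning. The point is therefore a suggested improvement and does not put the study's validity in doubt.

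**What to change.** Replace the sentence on repeated-measures ANOVA with a linear mixed model fitted by REML to all available samples. It should have exposure, visit and exposure × visit as fixed effects, allow for within-subject correlation, and use the infant's actual age at sampling for the last sample. Analyse log IgA if residuals are skewed. Report the exposure contrast at each visit. Apply the same model to fecal IgA and the other repeated continuous outcomes.

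State that milk contrasts at later visits apply to women still breastfeeding, because milk does not exist after weaning.

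The cost is one rewritten sentence and slightly more analysis work, with no new data or visits; the Stata version named in the article can fit the model. The price in assumptions is that missing samples are missing at random given the observed ones.
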